##### Between weeks 5–6 post-randomisation

Second workshop/telephone intervention is again broken down into sections and topics. The ‘Making the LINX to rebuild my life’ wall play a central part to the workshop. It assists in consolidating the learning and builds further on the young adults’ strengths. The young adults are helped to understand resilience and the part it plays in spinning life’s plates. Day 2 includes further examinations into personal risk and protective factors; the role self-esteem plays in keeping us and others safe; and identifying how positive communication can support our goals and make amends. The second day also assists the workshop leaders and Navigators in understanding if there are any gaps in support, whether new goals need to be set, and what they need to ‘keep their wall in order.’

The workshops ideally involve a group of individuals and take place face to face in a neutral venue. However, this is a pragmatic RCT and is being undertaken during the COVID-19 pandemic, which has necessitated changes to delivery of the intervention via telephone or video conferencing. This flexible approach reflects routine delivery of the intervention: where the number of attendees is insufficient to run a workshop, telephone/video conferencing may be used in order to fit delivery within the caution timeframe. The mode of delivery of all aspects of the intervention are recorded for the study and as far as possible will be accounted for in the analysis. Full details of the differences between the LINX workshops and the LINX telephone intervention have been documented and are available in the full protocol. As far as possible, it is only the mechanism of delivery that changes, the principle aims of the intervention and the content remain constant.

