#### Content and delivery of Gateway intervention

##### Part 1: Initial assessment with a Navigator

Within 3–5 working days of their disposal, the Gateway Navigator will conduct a detailed needs assessment with the participant and mentor them through the programme. Based on the identified needs, the Navigator will connect the young adult with the appropriate services (e.g., alcohol, drugs, mental health and/or housing). The Gateway Navigators are trained support/case workers, provided by third sector organisation No Limits, and Southampton City Council. Assessments are held face to face whenever possible, but where necessary they are carried out via phone or video calls. Subsequent contacts are predominantly via telephone, text or video calling. Some additional face to face contact may take place based on risk factors and considering COVID-19 guidance and precautions. This would be in informal settings such as coffee shops or public outdoor locations.

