### Sample size {14}

There is no widely accepted and established minimal clinically significant difference for the primary outcome, WEMWBS. It has been suggested that a change of three or more points is likely to be important to individuals but different statistical approaches provide different estimates ranging from three to eight points (WEMWBS user guide [22]). There is also variation in the standard deviation of the WEMWBS with estimates ranging from 6 to 10.8 [30] with the pooled estimate of 10 across all studies. Assuming 90% power, 5% 2-sided statistical significance, mean difference of 4 points on WEMWBS and a standard deviation of 10, 266 participants are required. Preliminary figures from The Hampton Trust’s skills/attitudes workshops for domestic abuse (RADAR intervention) suggests a drop-out rate of approximately 15%. Conservatively, assuming a 20% attrition rate, 334 participants would need to be recruited and randomised.

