## Assignment of interventions: allocation

### Sequence generation {16a}

Participants will be allocated using simple randomisation with a 1:1 allocation ratio. The allocation sequence will be created using computer-generated random numbers in Alchemer using a randomisation sequence approved by the trial statistician. The system was tested and verified by York Trials Unit (YTU) data management and the trial statisticians during the training of police investigators, prior to the start of recruitment to the study.

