## Statistical methods

### Statistical methods for primary and secondary outcomes {20a}

A detailed statistical analysis plan (SAP) will be agreed with the TMG and SSC/DMEC before all of the data have been collected. Amendments to the SAP will be agreed and clearly stated and justified. Analyses will be carried out using Stata v17 or later and follow the principles of intention-to-treat with outcomes analysed according to randomised group unless otherwise specified. Parameter estimates will be presented with associated 95% confidence intervals and *p* values, and significance testing will be two-sided at the 5% level unless otherwise stated.

The primary analysis will compare WEMWBS between treatment groups at 12 months and will be analysed using a covariance-pattern mixed-effect linear regression model, including assessments at 4 weeks, 16 weeks and 12 months post-randomisation, and treating participants as a random effect in order to account for repeated measurements amongst participants. Treatment group, time, group by time interaction, the total of the number of Record Management System (RMS) incidents and the number of Police National Computer (PNC) convictions 1 year pre-randomisation, age at randomisation, Index of Multiple Deprivation quintile at randomisation, pandemic time period and standard of usual process available will be adjusted for as fixed effects. If feasible, recruiting site will be included as a random effect. Pandemic time period refers to whether the follow-up took place before, during or after the COVID-19 pandemic, while standard of usual process available refers to the variation in the types of caution available during the pandemic. The inclusion of these two covariates reflects the guidance provided by Cro and colleagues for handling missing outcome data in randomised trials affected by the pandemic [33]. The treatment effect estimate at 12 months will be presented in the form of an adjusted mean difference, alongside the associated 95% confidence interval and *p* value. The treatment effect estimates at 4 weeks and 16 weeks will be presented in a similar manner as secondary outcomes.

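### The sample size and primary model make no allowance for possible clustering by Navigator or workshop group in the Gateway arm; if outcomes correlate within these clusters, the standard error would be too small and power at 266 evaluable below 90%

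*Protocol article*

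**What the plan says.** Delivery. Under Part 1 of the intervention description, "the Gateway Navigator will conduct a detailed needs assessment with the participant and mentor them through the programme". Navigators come from two organisations. Of the LINX sessions the protocol says "The workshops ideally involve a group of individuals and take place face to face in a neutral venue", and it then explains that telephone or video may be used instead, both because of the pandemic and routinely when too few people attend. No Navigator or LINX group is described for the usual-process arm.

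Sample size {14}. "Assuming 90% power, 5% 2-sided statistical significance, mean difference of 4 points on WEMWBS and a standard deviation of 10, 266 participants are required" and then "Conservatively, assuming a 20% attrition rate, 334 participants would need to be recruited and randomised". No ICC or design effect is mentioned.

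Allocation {16a}. "Participants will be allocated using simple randomisation with a 1:1 allocation ratio". Individuals are randomised, so any clustering arises from delivery.

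Primary model (Statistical methods {20a}). The model is described as "treating participants as a random effect in order to account for repeated measurements amongst participants", and "If feasible, recruiting site will be included as a random effect". There is no term for Navigator or workshop group. The intervention section undertakes to account for mode of delivery as far as possible, but mode does not identify who delivered the programme or which group a participant joined.

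**The concern.** When one arm receives its treatment through shared staff or groups, people with the same Navigator or group can end up with more similar outcomes than people with different ones. The variance of that arm's mean then exceeds what independence implies. The participant random effect deals with repeated measures on one person. A site effect common to both arms does not represent variation between Navigators or groups that exists only in the Gateway arm.

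At stake are the confidence interval and p value for the 12-month difference, which would be too narrow and too small, and the 90% power figure, which would be too high. All of this is conditional on a positive correlation at 12 months.

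**Working it through.** **Inputs from the protocol (Sample size {14}):** difference 4, SD 10, two-sided 5%, 90% power, 266 evaluable (133 per arm), 20% attrition, 334 randomised.

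**Inputs assumed, because the protocol gives none:** m evaluable participants per cluster in the Gateway arm, and ICC 0.01 to 0.05. Eight Navigators give m = 133/8 = 16.6; four give m = 133/4 = 33.25. All 133 Gateway participants are placed in equal clusters and controls are taken as independent.

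**Step 1: the plan's own figure.** The normal approximation gives (10 × (1.960 + 1.282)/4)² × 2 = 65.67 × 2 = 131.3, so 132 per arm. The t-based calculation gives 133 per arm (power 90.1%; 132 gives 89.9%), which is 266. Attrition: 133/0.8 = 166.25, so 167 per arm, or 334. Both figures reproduce with no design effect.

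**Step 2: clustering in one arm.**
- Design effect in the Gateway arm: DE = 1 + (m − 1) × ICC
- Standard error of the difference: SE = 10 × √((1 + DE)/133); under independence 10 × √(2/133) = 1.226
- Power of a 5% test that uses the correct SE: Φ(4/SE − 1.96), which is 90.4% at DE = 1
- Type I error of an analysis that assumes independence: 2 × P(Z > 1.96 × 1.226/SE)

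Example, 8 Navigators and ICC 0.02: DE = 1 + 15.625 × 0.02 = 1.3125; SE = 10 × √(2.3125/133) = 1.319, which is 7.5% above 1.226; power = Φ(3.03 − 1.96) = 86%; type I error = 2 × P(Z > 1.82) = 6.8%.

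| Cluster size | ICC | SE increase | Power, correct SE | Type I error, independence assumed |
|---|---|---|---|---|
| 4 | 0.01 | 0.7% | 89.9% | 5.2% |
| 4 | 0.05 | 3.7% | 88.2% | 5.9% |
| 8 | 0.02 | 3.4% | 88.4% | 5.8% |
| 8 | 0.05 | 8.4% | 85.3% | 7.1% |
| 16.6 (8 Navigators) | 0.01 | 4% | 88% | 5.9% |
| 16.6 | 0.02 | 8% | 86% | 6.8% |
| 16.6 | 0.05 | 18% | 79% | 9.6% |
| 33.25 (4 Navigators) | 0.01 | 8% | 86% | 6.9% |
| 33.25 | 0.02 | 15% | 81% | 8.8% |
| 33.25 | 0.05 | 34% | 68% | 14.5% |

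Simulation (20,000 runs per scenario, analysed as independent) gave type I errors of 9.6% for 8 Navigators and 14.5% for 4, both at ICC 0.05, in agreement with the formula.

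**Step 3: how much slack there is.** With 133 per arm, 90% power needs 1 + DE ≤ 133/65.67 = 2.025, so DE up to about 1.025. With 15% attrition, 334 × 0.85 ≈ 284 remain (142 per arm). Power under independence is then 92.1%, and DE may reach 142/65.67 − 1 = 1.16 before power drops under 90%.

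**The case against.** A reader might infer that the standard error is wrong as planned and that 90% power is lost. The protocol does not support that. Both need a positive ICC at 12 months and clusters of some size, and it states neither. Group attendance is an ideal with telephone or video as the alternative, so workshop clustering may touch only some participants. That each Navigator serves several participants is a reasonable inference, but caseloads are not given. Any Navigator effect may also fade between the end of the 16-week caution and 12 months. With small clusters and ICC 0.01–0.02 the loss against the 90% target is under 2 points. The power calculation takes no credit for covariates or repeated measures. These points stand, and they are why the concern is conditional.

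The attrition argument stands only in part. The other programme's workshop figures cited by the protocol "suggests a drop-out rate of approximately 15" per cent, and at that rate modest clustering would be absorbed. The plan itself assumes 20%, however, and extra participants do not correct a standard error computed as if observations were independent.

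It is also tempting to say that controls have no clusters at all. The Conditional caution section lists victim awareness, drug and alcohol courses run by various organisations, and does not say whether these are taught in groups. Treating controls as independent is a working assumption.

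Finally, sensitivity analyses are usually left to the SAP, which is not shown and may already contain this one. The article does, however, fix the primary model down to its random effects and derives its sample size under independence. The point concerns those stated choices.

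**Conclusion.** The point holds in conditional form. As stated, neither the sample size nor the primary model allows for correlation among Gateway participants who share a Navigator or workshop group. If the ICC is zero, the plan's figures stand. If it is positive, the standard error would be too small, and at 266 evaluable almost any such correlation takes power below 90% (DE above about 1.025).

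The size cannot be fixed from the protocol. Under the assumed values it is minor for clusters of 4 to 8 with ICC 0.01–0.02 (about 88–90% power). It becomes material for eight Navigators with ICC 0.02–0.05 (about 86–79% power, 6.8–9.6% type I error). Four Navigators with ICC 0.05 (68% and 14.5%) marks the far end of the range and should not be read as an expected result. The power figures use a normal reference distribution; small-sample degrees of freedom with few Navigators would lower them further.

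**What to change.** 1. Confirm that Navigator and workshop group can be linked to each Gateway participant. LINX attendance registers exist. The section on adherence {11c} does not list Navigator identity among the fields of the engagement spreadsheet, so it should not be assumed to be held; record it if it is absent. With 163 of 334 randomised at the time of writing, it can be captured prospectively for the remainder.
2. Unless the SAP already has it, add a sensitivity analysis of the primary outcome with a random effect for Navigator or workshop group in the Gateway arm only (partially nested), arm-specific residual variance and small-sample degrees of freedom, with each control treated as their own cluster.
3. Report the estimated ICC with the numbers of clusters and their sizes.
4. State in the sample-size section that the 90% power assumes no clustering in the Gateway arm.

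The cost is one extra model, one sentence and possibly one additional data field. With few Navigators the ICC will be imprecise, which is why this is proposed alongside the primary analysis. The primary model and the target of 334 do not change.

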#### Provision of Gateway intervention

The Gateway Navigators are provided by No Limits, a third sector organisation that provides free advice, counselling, support and advocacy for under 26-year-olds, and by Southampton City Council. Agencies accessed following the triaging of needs include The Prince’s Trust, Two Saints (housing) and local Community Mental Health Teams.

The Hampton Trust are a third sector organisation, established in 1996 whose staff have extensive skills and expertise in developing community-based interventions for adults and young people including the LINX workshops, which they facilitate.

### Criteria for discontinuing or modifying allocated interventions {11b}

#### Custody sergeant prerogative

Duty Custody Sergeants approve all disposals and have the final say over whether someone can be randomised. They have all received training and understand the implications for the trial should they over-turn the disposal for a study participant.

#### Breach of conditions

Participants who are randomised to receive the intervention but who breach their Gateway Conditional Caution and are referred back for potential prosecution for their original offence will continue to be approached for data collection. When a caution is breached, discretion may be applied for the intervention and this involves use of a standardised decision flow chart. Where individual circumstances warrant it and discretion is applied, the individual is permitted to remain within the Gateway programme.

Similarly for control group participants who breach the conditions of a caution, standard police procedure is followed where discretion may be applied or the individual referred back for prosecution of their original offence.

#### Withdrawal from study (change of status)

Participants will be free to withdraw from the study at any point without giving a reason. Each PIS gives information on how a participant can withdraw, including who to contact. Forms for documenting type and reason of withdrawal and other applicable change of status categories are available for use by the Police Gateway Team and the University of Southampton (UoS) researchers.

Participants who withdraw from the study after giving Stage 1 consent but before giving Stage 2 consent will have their study details wholly anonymised by the University researchers where any personal details have been shared via Huddle. For analysis purposes, they will be continue to be treated as randomised to their allocated groups.

Participants who consent to Stage 1, but not to subsequent Stage 2 (without withdrawing), will not have any study assessments performed.

For participants who withdraw following Stage 2 consent, information already obtained up to that point will be retained. To safeguard the individual’s rights under UK GDPR only the minimum personally identifiable information will be retained by the Universities. Personal data will remain on Huddle, managed by HC, but no longer visible to the researchers and will not be downloaded or processed for the purposes of the study. Participant withdrawal after Stage 1 consent will require completion of a Change of Status CRF by the researchers.

Participants who decide to withdraw from the study at any stage will not undergo any further follow-up related to the study.

#### Loss of capacity during participation in the study

Should a participant lose mental capacity after consenting to take part, they will be withdrawn from the study.

### Strategies to improve adherence to interventions {11c}

Spreadsheets within Huddle provide the Police Gateway Team with oversight of the number of active clients in Gateway, numbers breached, number completed, indicators of breaches/completers, time to date in Gateway and time before breached, discretions applied, monthly recruitment and the numbers refusing participation and cases missed.

An ‘Engagement with client’ spreadsheet is maintained by Navigators to record adherence data and is available in Huddle. This spreadsheet includes participant ID; type of contact, date of contact, whether participant responded to contact, duration of contact in minutes, name of referring agency and comments from the Navigator. Third sector organisations liaise directly with the Police Gateway Team and Navigators to report engagement updates in accordance with referrals.

The Hampton Trust provide attendance registers for the LINX workshops/video/calls as these are mandatory sessions for the intervention.

Standard police monitoring of adherence to alternative conditional cautions issued to participants in the usual care group are followed and the information about the conditions and any breaches will be included in the results.

### Relevant concomitant care permitted or prohibited during the trial {11d}

There are no restrictions on concomitant care. For participants receiving the Gateway caution, an undertaking not to re-offend during the length of the caution is required. There are no other prohibitions related to the trial.

### Provisions for post-trial care {30}

There are no provisions within the study for post-trial care.

### Outcomes {12}

#### Primary outcome measure

The primary outcome measure is the Warwick-Edinburgh Mental Well-being Scale (WEMWBS) at 12 months. This is used to measure health and well-being amongst study participants. WEMWBS is a 14-item self-reported questionnaire that addresses mental health and well-being and has established valid reliable psychometric properties in adolescent populations [21, 22]. Compared to other well-being indices, WEMWBS was tested for response bias and showed low correlation with both subscales of the Balanced Inventory of Desirable Responding: Impression Management (*p* = 0.18*) and self-deception (*p* = 0.35**), which make it suitable for self-report [23]. Participants will self-report WEMWBS at 4 weeks, 16 weeks and 1 year post-randomisation (**p* < 0.05, ***p* < 0.01).

#### Secondary outcome measures

The following are the secondary outcome measures:
WEMWBS at 4 and 16 weeks post-randomisation.The SF-12 will be used to report health status. The 12 items of the SF-12 provide a representative sample of the content of the eight health concepts [24] and the various operational definitions of those concepts, including what respondents are able to do, how they feel and how they evaluate their health status.Risky alcohol use will be measured using the Alcohol Use Disorders Identification Test (AUDIT). The AUDIT tool is a simple screening tool that is used to identify the early signs of hazardous and harmful drinking and mild dependence. AUDIT has been validated amongst an adolescent [25, 26] and collage age population [27].Drug use will be measured using the Adolescent Drug Involvement Scale (ADIS). The ADIS was deemed most appropriate, as it captures recent/current use, and has been validated within this population age group [28].Reoffending type and frequency through access to routine data: police records will be used to examine the type and frequency of the trigger and subsequent offences up to 1-year post-randomisation.Data on resource use, including access to primary and secondary care health services and social care, will primarily be used to inform cost consequence analysis. Data will be obtained through self-reported responses to questions in the CRFs based on the customised Client Service Receipt Inventory [29].

### Participant timeline {13}

The time taken to complete investigations to initial discussion about entering the study at Stage 1 and then to disposal, when a participant has been randomised, can vary so timelines for this phase are necessarily flexible (Figs. 1, 2 and 3). The causes of delays in the process will be documented.

**Fig. 3 Fig3:**
[figure not shown]
Gateway study flow chart

Participation in the intervention is for 16 weeks from the time of disposal.

Alternative conditional cautions issued to participants in the control arm will last a maximum of 16 weeks. For control arm participants allocated to a court summons, the timing will be variable, even more so as the pandemic has resulted in a backlog of cases. There will be more variability here such as the day the summons was raised, investigation completeness and if the disposal decision is made, in relation to the court date given.

For the study, all participants are asked to take part in telephone interviews at 4 weeks, 16 weeks and 1 year post-randomisation, with flexibility on timing anticipated to accommodate the target population. Participants missing one of the data collection points are followed up at the subsequent timepoint unless they have formally withdrawn from the study.

